##### Measurement of agility and balance

The Timed up and go test will be employed to assess patients’ agility as it has been done before in breast cancer patients [95]. For its performance, a chair will be placed against the wall and a cone will be placed in 3 m from the front edge of the chair to the back of the cone. The patient will sit in the middle of the chair keeping her back straight, her hands on her thighs and both feet on the floor. At the "go" signal, the participants will get up from the chair and walk as fast as possible to the cone, and around the cone, back to the chair. The time taken to complete the test will be recorded. The test will be repeated twice, and the best score achieved.

The One-leg stand test belonging to the ALPHA battery in adults [96] will be used to evaluate static balance. To do this, the patient will be placed in monopodal support, placing the sole on the inside of the knee. The test will be performed first with the right feet on the ground and then with the left. Patients will be able to use their arms to balance only when necessary.

##### Lower and upper body flexibility measurement

Hamstring flexibility will be measured using the V Sit and Reach test [8] where the participant will be seated on the floor with knees fully extended and feet 30 cm apart. Place a tape measure on the floor, equidistant between the feet, placing the 0 cm in line with the heels. Putting the palms of the hands together and keeping the elbows fully extended, the participants will bend their trunks as much as possible on the tape measure. The missing centimetres or the centimeters that are passed from their maximum bending point and the 0 cm will be noted.

Upper body flexibility will be evaluated by utilizing the Back scratch test, previously used in breast cancer patients [95] and belonging to the Senior Fitness Test battery [76]. During the test, the participants will be placed in a standing position, having to try to reach above their head, with their arm in flexion and external rotation, to touch their other hand, which will be placed on their back in supine position with the arm flexed [95]. The test will be performed first with the arm through which the chemotherapy was administered and then repeated with the other arm.).

#### Psychosocial and physical exercise outcomes

Psychological variables will be assessed utilizing self-administered questionnaires specifically validated for cancer patients.

##### Health-related quality of life measurement

To assess HRQoL patients will complete the European Organisation for Research and Treatment of Cancer Quality of Life Questionnaire (EORTC QLQ-C30) [97] which includes functional and cancer-specific symptom assessment and the results will be analyzed following the instructions given in its manual [98]. Concretely, the QLQ-C30 is composed of both multi-item scales to assess functional, symptoms and global health status and six single-item measures to score the left symptoms. Inside the functional outcomes, 6 items correspond to physical function, 2 to functional role, 4 to emotional function, 2 to cognitive function and 2 to a social function. Moreover, the assessed symptoms will be fatigue (3 items), nausea and vomiting (2 items), pain (2 items), dyspnoea (1 item) insomnia (1 item), appetite loss (1 item), constipation (1 item), diarrhea (1 item) and financial difficulties (1 item). All the scales and single-item measures range in score from 0 to 100. A high scale score represents a higher response level. Thus, a high score for a functional scale represents a high/healthy level of functioning, a high score for the global health status / QoL represents a high QoL, but a high score for a symptom scale/item represents a high level of symptomatology/problems [23].

##### Cancer-related fatigue measurement

For the assessment of cancer-related fatigue, the fatigue subscale of Functional Assessment of Chronic Illness Therapy- Fatigue questionnaire [99] will also be used and analyzed according to the instructions of its creators [100]. The questionnaire is composed of 13 items where participants would answer a Likert scale of 4 points being 1 “Not at all” and 4 “Very much”. The questions are asked about perceived fatigue in the last 7 days. The score could range from 0 to 52, so that, higher scorings represent high fatigue symptoms.

##### Life satisfaction, self-esteem, depression and anxiety measurements

Life satisfaction will be assessed using the Satisfaction With Life Scale questionnaire [101], validated in Spanish breast cancer patients [102]. The scale is composed of 5 items to answer with a Likert scale from 1 to 5 being 1 “strongly disagree” and 5 “strongly agree”. Higher scores mean higher satisfaction with life [101]. In addition, the Rosenberg Self-Esteem Scale [103] employed before in cancer patients [104] will be utilized for analyzing Spanish breast cancer patients’ self-esteem. The scale, validated in Spanish [105], comprises ten items with a Likert scale of four options. According to the sum of their items, the scale is divided into three ranges: normal or high self-esteem (between 30 and 40 points), medium self-esteem (26–29 points), and low self-esteem (< 26 points). It has a Cronbach’s alpha of 0.87 and a reliability of 0.74 [105].

In addition, the Hospital Anxiety and Depression (HAD) Scale will be used and analyzed according to the authors' indications [106]. This questionnaire was validated in Spanish oncological patients to obtain results regarding anxiety and depression [107]. The HAD scale consists of 14 items referring to participants’ perceptions regarding the last week. The odd-numbered items make up the anxiety subscale and their response scale are scored from 3 to 0. The even-numbered items make up the subscale of depression and are scored from 0 to 3. The total score in each subscale is obtained by adding the scores of the corresponding items, with a range each from 0 to 21. In both cases, the higher the score, the higher the level of anxiety or depression [106].

##### Shoulder mobility disability and kinesiophobia measurements

For the assessment of their perception of disability due to shoulder mobility so common after breast cancer treatment, the Quick Disabilities of the Arm, Shoulder and Hand questionnaire will be used [108, 109]. The scale is composed of 11 items graded from 0 to 100 asking patients to rate the level of difficulty and pain in performing several tasks over the past week. Patients will answer each question scoring from 1 to 5 selecting 1 when the activities are performed with no difficulty and 5 for those activities unable to perform with “extreme difficulty”. Relatedly, fear of movement will be measured using the 11-items Tampa Kinesiophobia Scale [110, 111]. The scale has two subscales, one focused on activity avoidances (reflecting the belief that activity may result in injury or increased pain) and the other concerning somatic focus (indicating the belief in underlying and serious medical problems). The total score ranges from 11–44 points with higher scores indicating greater fear of pain, movement, and injury [111]. Items on the TSK-11 are scored from 1 (strongly disagree) to 4 (strongly agree) [111].

##### Physical activity and motivation for exercising measurements

Finally, the International Physical Activity Questionnaire be administered to evaluate the level of physical activity of the patients in the assessment periods [112]. The 8 questions refer to the time patients spent being active in the last 7 days to analyze the time spent in making low-intensity activities, moderate-intensity activities, high-intensity activities and sedentary activities [112]. In addition, the existence or not of behavioral change/motivation towards exercise will be assessed using the Behavioural Regulation of Exercise Behaviour Scale—2 [113]. This questionnaire is composed of a 19-item scale with five factors (amotivation, external, introjected, identified and intrinsic motivation) [114]. Patients will reflect their opinion by a Likert scale from 1 to 5 corresponding 1 to “strongly disagree” and 5 to “strongly agree”.

### Statistical analysis

All the outcome results will be included in an anonymous database to conduct the statistical analyses. A descriptive, quantitative, and graphics analysis will be performed of all the included variables. The statistic software employed will be the IBM Statistical Package for the Social Sciences (version 25.0; SPSS, Inc., Chicago, IL, USA) [115]. The number of statistical analyses will be high and diverse depending on the nature of the results. In general, we will proceed with the usual steps to check the normality and homogeneity of variables.

First, the Kolmogorov–Smirnov and Shapiro Wilk tests will be used to determine whether parametric or non-parametric statistical analyses should be applied to each of the variables analyzed. In this regard, normal distribution will be assumed when the p-value is greater than 0.05 indicating that the variable tested was not significantly different from a normal distribution. Descriptive results will be presented as mean and SD or median (range) according to the results of the normality tests. Subsequently, to evaluate the effects of the program, a repeated-measures ANOVA or Kruskal–Wallis, depending on the normal distribution, will be used. The interaction factors of the ANOVA, or Kruskal–Wallis, will be the group (HRVG, PEG or CG) and the timing of the measure (before, after the intervention and follow-up). Besides, a Bonferroni analysis will be performed to adjust the results. Results shall include the Cohen’s d effect size (95% confidence interval) and statistical significance for each dependent variable concerning time and its interaction effects (group × time). Moreover, to analyze the differences between the group independently in each of the variables, the T-test for Independent Samples and the T-test for related samples, or a Mann–Whitney U-test or Wilcoxon in case of not fulfilling the principle of normality, will be employed.

Concurrently, a correlation analysis is planned to be done to establish novel relations between some of the measures performed. For instance, a Pearson o Spearman analysis (depending on the results of the normal distribution analysis) will be calculated between the change in strength, the body composition, cardiotoxicity variables and the psychological variables. Moreover, a correlation between the results obtained in the different questionnaires will be calculated.

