#### Sample size

Given that, to our knowledge, no previous studies have examined the effects of an exercise program guided by daily HRV in breast cancer patients and its comparison to a moderate to high-intensity exercise group and a control group, the sample size was calculated by considering the exercise intensity differences between groups. In this regard, we have taken as reference values interventions carried out with three groups, a high-intensity group, a moderate-intensity group and a control group. Moreover, the oxygen consumption peak (VO_2peak_) has been selected to make the calculations due to its importance in cardiovascular and physical health. The chosen tool to analyze sample size has been using G-Power 3.1 and the calculation were done basing us on the data from the investigations carried out by Martin, Battaglini [46] and Northey, Pumpa [47] two different studies. In both cases, between-group significant differences were reported.

A total of 18 patients, (11 allocated to the experimental and 11 allocated to the control group) would be needed in the worst of the cases to achieve a 99% statistical power for VO_2peak_. Moreover, regarding the low number of participants obtain, the calculations concerning the effects of exercise in Global Longitudinal Strain (GLS) compared to a control group were also done. In this case, the data employed for the calculation was from Costello, Roberts [48] where significant differences within and between groups were achieved. So, in the prior calculations performed, we would need a total of 50 patients [25 in each group] to achieve a 99% statistical power (two tails). Therefore, assuming 20% of dropouts, 90 patients will be recruited and allocated to one group or the other. Due to the large number of patients that are estimable to be enrolled in the study, the recruitment and intervention will be carried out progressively over 24 months depending on the number of patients to be recruited.

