### Interventions

#### Physical exercise programs

First, the common aspects between the two exercise groups are going to be mentioned, to explain afterwards the peculiarities of each physical exercise program. The programs of both experimental groups, PEG and HRVG, will last 14 weeks, and patients will train three times per week. All sessions will be supervised and remote. So that, each patient will connect with the physical exercise professional and with the other 4 participants by videocall. Moreover, the practitioner will monitor their heart rate in real-time because each patient will be given a MyZone heart rate (HR) control and platform access to MZ-Remote. In this way the professional will be able to adjust their workout intensity according to their HR, in the cardiovascular exercises and the weightlifting load in the resistance exercises; and to control and correct, participants’ posture and technique. Moreover, these measures will be determinant to asses participants’ exercise adherence. During the sessions, participants will be able to see their HR and HR of the rest of their training group. In addition, to promote social interaction an extra link will be given to those patients which want to see each other while practicing exercise. The necessary material to perform the exercise programs will be given to each participant in the before-intervention evaluation. This training kit will include a barbell of 2 kg, 2 weight discs of 5 kg, 2 weight discs of 2.5 kg, 2 weight discs of 1.25 kg and a Myzone's MZ-3 Belt chest strap.

Each session will last approximately 60 min and will include a warm-up, a main part composed of cardiovascular resistance exercises and a cooldown. The warm-up, lasting from 5 to 10 min, will include upper, lower body and truck mobility, and core muscular activation. The cooldown part will last about 5 min and will combine stretching of the muscles involved during the corresponding session. Moreover, during the stretches, breathing feedback will be given to fully relax and enhance elongation during the exhalation phase.

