### Outcomes

The following outcomes will be assessed in person by the oncology group at the hospital (Marqués de Valdecilla Hospital) or by a physical exercise professional at the sports center (GOfit) when it corresponds. The evaluations will be carried out before, after the intervention and 3 and 6 months after the end of the intervention to all the participants (HRVG, PEG and CG). To ensure CG measurements and follow up evaluations the principal investigator will call or write participants each month.

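### The planned repeated-measures ANOVA treats baseline as a time level and, as usually run, keeps only complete patients; a baseline-adjusted mixed model would make better use of the same data

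*Protocol article*

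**What the plan says.** All places are in the protocol article.

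- **Statistical analysis.** For programme effects, "a repeated-measures ANOVA or Kruskal–Wallis, depending on the normal distribution, will be used". The factors are group and "the timing of the measure (before, after the intervention and follow-up"), so the pre-intervention measurement is a level of the time factor. The results to be given are Cohen's d with its interval and "statistical significance for each dependent variable concerning time and its interaction effects (group × time"). A Bonferroni step and separate independent-samples and paired t-tests (or rank-based counterparts) follow. The software is "IBM Statistical Package for the Social Sciences (version 25.0"). No baseline covariate or training-group term is named.
- **Outcomes.** "The evaluations will be carried out before, after the intervention and 3 and 6 months after the end of the intervention", which makes four assessments.
- **Sample size.** The total of 90 is reached "assuming 20% of dropouts".
- **Physical exercise programs.** In the two exercise arms, "each patient will connect with the physical exercise professional and with the other 4 participants by videocall".
- **Randomization and allocation.** Patients are allocated before the baseline assessments take place.

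**The concern.** The named method fits this design poorly in three ways.

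1. **Missing visits.** Classical repeated-measures ANOVA needs a full row per patient. Someone assessed after the programme but absent at month 6 would normally drop out of that model altogether. Power falls, and the result is biased if completing follow-up depends on arm, fatigue or cardiac status.
2. **Baseline.** Treating it as a time level amounts to analysing change from baseline, which uses its predictive value less efficiently than a covariate does. The interaction test is also an omnibus test: with three arms and, if all four visits enter, it has (3 − 1) × (4 − 1) = 6 degrees of freedom. It does not deliver an adjusted HRVG–PEG difference at the end of the programme.
3. **Live training groups.** Patients who train together with one professional may have correlated outcomes. An analysis that treats them as independent could then give intervals that are too narrow.

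**Working it through.** **Inputs.** From the article: 90 patients, three arms, 25 per group before dropout, 20% dropout, four visits, training groups of five. Assumed, because the article gives no figure: equal allocation (30 per arm), two-sided alpha 0.05, equal variance at each visit, a common correlation rho between visits, and an ICC for training groups.

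**The plan's own total.** 3 × 25 = 75, and 75 × 1.2 = 90, so the stated total is reproduced. Losing 20% leaves 90 × 0.8 = 72, or 24 per arm. That is the complete-case set if each dropout misses at least one visit.

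**Baseline adjustment.** The variance of change from baseline is 2σ²(1 − rho). The variance after adjustment is σ²(1 − rho²). Their ratio is (1 + rho)/2. Against a t-test on the post-intervention value alone, the ratio is 1 − rho².

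| rho | adjusted ÷ change score | variance cut | adjusted ÷ post value alone |
|---|---|---|---|
| 0.3 | 0.65 | 35% | 0.91 |
| 0.5 | 0.75 | 25% | 0.75 |
| 0.7 | 0.85 | 15% | 0.51 |
| 0.9 | 0.95 | 5% | 0.19 |

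**Partial follow-up.** Suppose half of the dropouts leave before the post-intervention visit and half after it but before month 3. Then 27 per arm, not 24, inform the post-intervention contrast. The ratio against complete-case change scores becomes (1 + rho)/2 × 24/27: 0.67 at rho 0.5 and 0.76 at rho 0.7. If all losses come before the post-intervention visit, nothing is gained beyond baseline adjustment.

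**Training groups.** Suppose each call holds one arm only. The design effect for HRVG vs PEG is 1 + (5 − 1) × ICC, and the actual error of a nominal 5% test that ignores it is 2 × P(Z > 1.96/√DE).

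| ICC | DE | actual error |
|---|---|---|
| 0.01 | 1.04 | 5.5% |
| 0.05 | 1.20 | 7.4% |
| 0.10 | 1.40 | 9.8% |

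**Net effect on HRVG–PEG precision.** With 30/5 = 6 groups per exercise arm, a model with the group term has about 12 − 2 = 10 degrees of freedom (critical t 2.228). The planned analysis has 24 + 24 − 2 = 46 (critical t 2.013). At rho 0.7 and the dropout pattern above, the interval width relative to the planned analysis is √(0.756 × DE) × 2.228/2.013: 0.98 at ICC 0.01, 1.05 at 0.05 and 1.14 at 0.10.

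**The case against.** **Missing-data rules may sit in a document not shown.** This stands in part. The article does not say that incomplete patients are excluded; that is how the method is usually run. Nor does its description of the time factor settle that all four visits enter one model. A reader might infer that every patient with a missed visit is certainly dropped, or that fewer than 72 remain. The first is not stated, and the second needs a missed-visit rate that the article does not give.

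**The separate t-tests can compare arms at the end of the programme without a month-6 value.** This stands. The end-of-programme contrast is not lost to the plan, but those tests make no use of baseline.

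**Listwise loss costs little power on the plan's own figures.** The stated 25 per group at 99% power implies d of about 1.24 at alpha 0.05. At that effect, 24 per arm gives 98.7% power against 99.7% with 30. That effect, however, is for exercise versus control, while the stated aim compares two exercise programmes. At an assumed d of 0.5, power is about 40% with 24 per arm and 48% with 30.

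**Repeated-measures ANOVA is a standard method in a randomised trial.** True. The baseline argument is about efficiency, not validity.

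**The covariate is measured after allocation.** True, and effort-based or self-reported baselines could shift if patients already know their arm. The planned group × time test uses the same baseline, so this qualifies the fix without favouring the ANOVA.

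**The training-group inflation is conditional.** A reader might take 5.5–9.8% as established. It is not: the article does not say whether a call holds one arm or mixes HRVG and PEG. In mixed calls the shared effect would largely cancel in that contrast.

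**Conclusion.** The point holds as a specific improvement to a method that the article fixes. Baseline is a time level with no covariate, the ANOVA as usually run would rest on about 72 of 90 patients, and no baseline-adjusted arm difference at the end of the programme is planned. Adjustment would cut variance by roughly 35% to 5% over rho 0.3 to 0.9. The use of partial follow-up adds to this only if some dropouts attend the post-intervention visit, and it relies on missing at random.

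A reader might infer that the better model is a free gain throughout. The arithmetic does not support that. The gain comes from baseline and partial follow-up. The training-group term protects the error rate and costs precision, so at ICC 0.05 and rho 0.7 the HRVG–PEG interval ends about 5% wider than planned. That term therefore belongs in a sensitivity analysis, with its size conditional on the ICC and on how calls are made up.

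**What to change.** For continuous outcomes, replace the repeated-measures ANOVA with a linear mixed model (SPSS MIXED):

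- **Responses:** post-intervention, 3-month and 6-month values.
- **Fixed effects:** arm × visit and baseline × visit. **Covariance:** unstructured.
- **Patients:** every randomised patient with a baseline and at least one follow-up value; state the missing-at-random assumption.
- **Key contrasts:** HRVG–PEG, HRVG–CG and PEG–CG at the end of the intervention, with intervals.
- **Baseline:** state that it is measured after allocation, and interpret adjustment for effort-based or self-reported measures with caution.
- **Sensitivity analysis:** add a random effect for the five-person video-call group in the exercise arms, and report whether calls mix arms.

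The rank-based branch needs its own wording, because Kruskal–Wallis is a one-factor test for independent groups and cannot test group × time.

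Cost: revised analysis text, slightly more programming, and a record of each patient's training group. No new patients or assessments are needed. The sensitivity model has only about 10 degrees of freedom for HRVG–PEG if calls hold one arm, so its interval may be wider.

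### For outcomes that fail the normality test, the plan asks Kruskal-Wallis for a group × time result that this test cannot give.

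*Protocol article*

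**What the plan says.** All references are to the protocol article.

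- **Routing rule (Statistical analysis).** Each variable is tested for normality, and "normal distribution will be assumed when the p-value is greater than 0.05". The programme effect is then evaluated as follows: "a repeated-measures ANOVA or Kruskal–Wallis, depending on the normal distribution, will be used".
- **Factors (same section).** "The interaction factors of the ANOVA, or Kruskal–Wallis, will be the group (HRVG, PEG or CG) and the timing of the measure". One sentence covers both tests.
- **Result promised (same section).** Reports are to include "statistical significance for each dependent variable concerning time and its interaction effects (group × time"), with no exception for outcomes on the non-parametric branch.
- **Other tests (same section).** Group differences are also to be examined with t-tests, "or a Mann–Whitney U-test or Wilcoxon in case of not fulfilling the principle of normality". For adjustment, "a Bonferroni analysis will be performed to adjust the results".
- **Visits (Outcomes).** Assessments take place "before, after the intervention and 3 and 6 months after the end of the intervention to all the participants", which makes four per patient.
- **Size (Sample size).** "assuming 20% of dropouts, 90 patients will be recruited", spread over three groups.

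**The concern.** Kruskal-Wallis compares several independent samples on one classification. It has no second factor, no interaction term and no means of allowing for repeated measurements on the same patient. Yet the plan names it as the substitute for a two-factor repeated-measures analysis and expects the same group × time output.

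The aim is to compare the effects of two exercise programmes and usual care, and group × time is the effect the plan chose to report for each outcome. For any outcome on this branch, that result either will not exist or will come from a test that answers a different question. If the substitute is picked only when the data are in hand, the choice is post hoc.

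**Working it through.** The plan states no figure to reproduce. The check is to run the sentence in each way it could be carried out and see what is tested.

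**Inputs from the documents:** 3 groups, 4 visits, 90 patients.

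**Assumptions:** 30 per arm (90 / 3; no allocation ratio is stated), nominal α of 0.05, within-patient correlation ρ equal across visits, and shifts in SD units on the log scale. Simulations used 2,000 to 3,000 trials per setting. Kruskal-Wallis uses ranks only, so a log transformation does not alter its result when it is applied to the visit values.

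**Degrees of freedom.** A group × time layout splits 12 − 1 = 11 degrees of freedom into group (2), time (3) and interaction (2 × 3 = 6). Kruskal-Wallis over 12 cells gives one statistic on all 11 and cannot isolate the 6. By group it has 2, and by time it has 3. None of these is the interaction.

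**Reading A: visits stacked by group (90 × 4 = 360 values treated as independent).** With no effect of any kind, correlation inflates the statistic by about 1 + (4 − 1)ρ. The 5% critical value on 2 df is 5.991, and P(χ² on 2 df > x) = exp(−x/2), so the error rate is about exp(−5.991 / [2(1 + 3ρ)]).

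| ρ | 1 + 3ρ | Approximation | Simulated |
|---|---|---|---|
| 0.3 | 1.9 | 0.207 | 0.206 |
| 0.5 | 2.5 | 0.302 | 0.293–0.304 |
| 0.6 | 2.8 | 0.343 | 0.335 |
| 0.7 | 3.1 | 0.380 | 0.371–0.379 |
| 0.9 | 3.7 | 0.445 | 0.454 |

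At ρ = 0 the simulated rate is 0.044, so the inflation comes from the correlation. With 25 per arm it is much the same: 0.307 at ρ = 0.5 and 0.375 at 0.7.

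**Reading B: 12 group-by-visit cells.** Rejection rates with no interaction, as ranges over the simulation runs:

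| Shift after baseline shared by all arms | Rejection rate |
|---|---|
| none | 4–8% |
| 0.2 SD | 8–11% |
| 0.3 SD | 17–22% |
| 0.5 SD | 70–76% |

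A constant 0.5 SD offset in one arm, again with no interaction, gives 69% at ρ = 0.5. A shared shift is plausible, because the eligibility criteria exclude patients who finished treatment more than 5 months earlier, so all arms may be recovering.

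**Reading C: by time, pooled over groups.** With no effect, the test rejects 1.2% of the time at ρ = 0.3, 0.2% at 0.5 and 0.0% at 0.7. It is very conservative and carries no information on groups.

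**Reading D: by group at one visit.** With no effect, it rejects 4–6% of the time. This is valid between randomised arms after baseline. A constant 0.5 SD offset that is already present at baseline gives 46%, which shows that it measures level and not difference in change.

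**Comparison: Kruskal-Wallis on each patient's change from baseline (log scale, first post-baseline visit).** Rejection was 4.2–5.5% in every setting without an interaction, including those with a shared shift or a baseline offset. The plan names no such analysis for programme effects; change scores appear only in the correlation analysis.

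**The case against.** The strongest reply is that valid inference on these outcomes remains. The same section plans Mann-Whitney comparisons, and between randomised arms at a post-baseline visit these are sound. So is Kruskal-Wallis by group at one visit, which is at least as natural a reading as stacking. This stands. A reader might infer that results on this branch are wholly invalid or leave the treatment effect untested. The documents do not support that: what is lost is the promised group × time result.

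The large error rates are also conditional. The article nowhere says to stack visits or to form 12 cells. In the 12-cell test with a real shared shift, the null of equal cells is false, so rejection is an error only if it is reported as an interaction. It would be wrong to quote 70–76% as the plan's error rate. This stands too, and is why the range is shown.

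The scope is uncertain. A reader might infer that the cardiotoxicity and inflammation markers will fail the normality test, but the article gives no distributions. Nothing shows that VO2peak or GLS, the outcomes behind the sample size, would fail. Outcomes that pass go to the ANOVA and are untouched.

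Finally, a reader might extend the point to normality pre-testing as such, on the ground that residuals should be tested and not raw values. The text does not say whether raw values, changes or residuals are tested. That is a separate criticism, and this point does not need it.

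Two replies fail. An analysis plan that is not shown does not excuse the sentence, because the article itself names the wrong test. The Bonferroni step corrects neither dependence between visits nor a missing interaction term.

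**Conclusion.** The rule is wrong as written. For outcomes that fail the normality test, it specifies a one-way test for independent samples and promises an interaction from four correlated visits.

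The size depends on execution. At a single visit, the interaction is untested while the between-arm comparison holds about 5% error. With stacked visits, false positives run at about 29–38%. With 12 cells, rejection ranges from near nominal to 70–76% as the shared shift grows from zero to 0.5 SD. These figures rest on the assumed correlation (0.5–0.7 for the stacked figure), 30 per arm and the assumed shifts.

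The test's inability to give group × time rests on none of these assumptions. High-sensitivity troponin, NT-proBNP and C-reactive protein are plausible candidates for this branch, but no more than that can be said.

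**What to change.** Delete Kruskal-Wallis with time as a factor. Before any data are analysed, name one method for non-normal outcomes that tests whether change over time differs between groups. Either of these would do:

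1. A mixed model with group × time on a log scale fixed in advance for the skewed markers (troponin, NT-proBNP, C-reactive protein).
2. Kruskal-Wallis on each patient's change from baseline at each follow-up visit, with the scale of the change stated (about 4–6% error in simulation).

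The single-visit Mann-Whitney comparisons can stay, described as between-arm tests and not as tests of interaction.

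The cost is small, since only the analysis wording changes. Under option 1, effects are reported as ratios. Option 2 gives three tests per outcome, one per follow-up visit, which the Bonferroni step should cover. Its power also depends on the correlation. With a simulated 0.5 SD benefit in both exercise arms, it rejected 33%, 46% and 71% of the time at ρ = 0.3, 0.5 and 0.7, against 47–48% for the single-visit comparison.

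The ANOVA for outcomes that pass the normality test need not be replaced for this repair.
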